### Data management and quality control

The initial data will be filled in case report forms (CRFs) by the responsible outcome assessor and immediately entered into the Electronic Data Capture (EDC) system provided by Lnkmed. The clinical research associates (CRAs) will conduct monitoring activities through the website every week to enhance the quality of trial. The CRFs will be required from the clinical sites when they accomplish all the recruitment, treatment, and assessment of participants. All data on the EDC system will be locked after confirmations are presented by two independent CRAs that data online are consistent with data in the CRFs. Any deviation from the study protocol will be reported in time.

Researchers in all clinical sites will be jointly trained by the principal investigator before we carry out the trial. Acupuncture treatments will be performed by licensed acupuncturists with at least 2 years of experience in clinical practice. Both TA and SA are safe for participants in our trial; thus, no intervention modification is permissible. Considering the management of AEs will be the same in either TA group or SA group and the trial will be suspended for all serious AEs, there will be no unblinding during the trial. Group allocation will be kept by Lnkmed and revealed after the completion of statistical analysis. Participants in the SA group will receive 12 sessions of supplementary TA treatment if they want. Withdrawals or dropouts will be clearly documented during the trial.

### Sample size

According to the unpublished preliminary data collected from 25 participants (12 in acupuncture group and 13 in sham acupuncture group) from our recent study, the response rate of acupuncture for 4 weeks was 83.3%, the response rate of sham acupuncture for 4 weeks was 69%. Calculations was performed based on two-tailed testing with a 5% alpha, a desired power set at 80%, and accounting for a 20% dropout rate after 4 months. The allocation ratio was 1, resulting in 170 participants in the TA group and 170 participants in the SA group.

### Statistics

The continuous data will be represented as means with standard deviations (SD) or medians with interquartile ranges (IQR). For normally distributed measurement data, changes in the variables from baseline will be examined by independent samples *t* test. For non-normal distribution data, nonparametric test will be used. The quantitative data will be presented as frequencies (number of cases) and relative frequencies (percentages). Categorical variables will be compared using the Chi-square (*χ*^2^) test or the Fisher exact test.

The primary outcome will be assessed in the full analysis set. The full analysis set will include all randomly assigned patients who received at least one session of treatment. Safety will be also assessed in this set. Missing data on the primary outcome will be imputed by using the multiple imputation method under the missing-at-random assumption.

All data analysis will be performed using SPSS V.20.0 (IBM SPSS Statistics; IBM Corp, Somers, NY), a two-tailed *P* value < 0.05 will be considered statistically significant.

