**Methods:**

This will be a sham-controlled, randomized, multi-center clinical trial. A total of 340 participants will be recruited and randomly allocated to either traditional acupuncture group or sham acupuncture group. All participants will receive 12 treatment sessions over 4 weeks and 2 follow-up assessments in the following 3 months at week 8 and week 16. The primary outcome will be the proportion of responders at week 5. Secondary outcomes will include visual analog scale, Australian Canadian Osteoarthritis Hand Index, Functional Index for hand OA, the number of symptomatic joints, hand grip strength and pinch strength, global assessment, the World Health Organization Quality of Life abbreviated version and expectations. Safety will be evaluated during the whole process of the trial. All outcomes will be analyzed following the intention-to-treat principle.

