### Secondary outcomes

Secondary outcomes will include VAS score on pain intensity, AUSCAN, Functional Index for hand OA (FIHOA), the number of painful joints, tender joints and swollen joints, hand grip strength and pinch strength, global assessment, the World Health Organization Quality of Life abbreviated version (WHOQOL-BREF) and the participants' expectations for acupuncture. As shown in Table 2, the outcome measurements will be assessed at baseline, week 5, week 8, and week 16 after randomization. A responsible research assistant will be assigned by each hospital to complete all outcome assessments during this trial. The research assistants will be blinded from group allocation.

**Table 2 Tab2:** Primary and Secondary Outcomes

Primary outcome	*Overall responder*	
	Showing 1 of the 3 followings: ≥ 50% decrease and absolute change ≥ 20 in VAS score on average pain intensity; ≥ 50% decrease and absolute change ≥ 20 in AUSCAN; ≥ 20% decrease and absolute change ≥ 10 in at least two measurements of VAS score on average pain intensity, AUSCAN and global assessment	Week 5
Secondary outcomes	*Overall responder*	
	Showing 1 of the 3 followings: ≥ 50% decrease and absolute change ≥ 20 in VAS score on average pain intensity; ≥ 50% decrease and absolute change ≥ 20 in AUSCAN; ≥ 20% decrease and absolute change ≥ 10 in at least two measurements of VAS score on average pain intensity, AUSCAN and global assessment	Week 8, week 16
	*Pain*	
	Change in VAS score from baseline on average pain intensity Change in VAS score from baseline on maximal pain intensity The proportion of participants with an at least 15-point decrease in VAS score from baseline on average pain intensity	Week 5, week 8, week 16
	*Physical function*	
	Change in AUSCAN total score from baseline Change in AUSCAN subscale scores including pain, stiffness and physical function from baseline Change in FIHOA from baseline	Week 5, week 8, week 16
	*Patient global assessment*	
	Change in patient global assessment of improvement from baseline	Week 5, week 8, week 16
	*Joint activity*	
	Change in the number of painful joints from baseline Change in the number of tender joints from baseline Change in the number of swollen joints from baseline	Week 5, week 8, week 16
	*Hand strength*	
	Change in hand grip strength from baseline Change in hand pinch strength from baseline	Week 5, week 8, week 16
	*Quality of life*	
	Change in WHOQOL-BREF from baseline	Week 5, week 8, week 16
	*Other outcomes*	

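### Continuous secondary outcomes are compared by an unadjusted t test on change, or an unnamed rank test if non-normal, which costs precision and leaves the estimated quantity open

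*Protocol article*

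**What the plan says.** The Statistics section of the protocol article sets the rule for continuous outcomes: "For normally distributed measurement data, changes in the variables from baseline will be examined by independent samples" t test. It continues: "For non-normal distribution data, nonparametric test will be used". The nonparametric test is not named, no criterion for normality is given, and no covariate is mentioned.

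Under Secondary outcomes, "the outcome measurements will be assessed at baseline, week 5, week 8, and week 16 after randomization". Table 2 lists at least 14 continuous changes: average and maximal VAS pain, AUSCAN total and its three subscales, FIHOA, patient global assessment, three joint counts, grip strength, pinch strength and WHOQOL-BREF. Each is assessed at weeks 5, 8 and 16, which gives at least 14 × 3 = 42 between-group comparisons under this rule. Randomization and allocation states that randomisation is stratified by centre.

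**The concern.** Two features of the rule matter.

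First, subtracting the baseline is not the same as adjusting for it. The difference takes away the whole baseline value whatever its actual relation to follow-up, and so carries baseline noise into the comparison. A model that estimates that relation is at least as precise in large samples. The baseline data are already collected, so the precision is given up for nothing. The stratification factor, centre, is also left out.

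Second, the observed distribution decides which test is used. A t test goes with a difference in mean change; a rank test compares the ordering of the two groups. The same outcome could be reported as a mean difference at week 5 and as a rank comparison at week 16, and the reader could not line the two up.

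At stake are the width of the intervals and the comparability of results across visits for pain, function, joint activity, strength and quality of life, which carry the trial's claims beyond the week 5 responder rate.

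**Working it through.** **Inputs from the article.** Two-sided alpha 5%; 80% power; 20% dropout; 170 per group; responder rates 83.3% and 69% (all Sample size).

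**Inputs not in the article, hence assumed.** The correlation ρ between baseline and follow-up, and the ratio k = follow-up SD / baseline SD. Both are shown over a range.

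**Step 1: the plan's own figure.** The article gives a sample size only for the binary primary outcome. With the unpooled two-proportion formula, n = (1.960 + 0.842)² × (0.833 × 0.167 + 0.69 × 0.31) / 0.143² = 7.849 × 0.3530 / 0.02045 ≈ 135.5, so 136 per group. Then 136 / 0.80 = 170, as stated. This confirms 136 completers per group as the planning figure. It says nothing about power for the continuous outcomes.

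**Step 2: variance of the two analyses.** Set the baseline SD to 1 and the follow-up SD to k.

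- Change score: V_change = 1 + k² − 2ρk
- Baseline-adjusted (ANCOVA): V_adj = k²(1 − ρ²)
- Difference: V_change − V_adj = (1 − ρk)², which is never negative
- Share of variance lost: 1 − V_adj / V_change

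With k = 1, V_change = 2(1 − ρ) and V_adj = (1 − ρ)(1 + ρ), so the ratio is (1 + ρ)/2 and the loss is (1 − ρ)/2.

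**Step 3: equal SDs (k = 1).** The last column takes 136 per group and an effect that the adjusted analysis would detect with 80% power, and gives the power of the change-score t test for that effect.

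| assumed ρ | variance lost | SE reduction from adjusting | power of change-score test |
|---|---|---|---|
| 0.3 | 35% | 19% | 62% |
| 0.5 | 25% | 13% | 68% |
| 0.7 | 15% | 8% | 73% |
| 0.8 | 10% | 5% | 76% |

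**Step 4: unequal SDs.** Share of variance lost:

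| assumed ρ | k = 0.8 | k = 1.2 |
|---|---|---|
| 0.3 | 50% | 24% |
| 0.5 | 43% | 13% |
| 0.7 | 37% | 3% |

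Worked example for the smallest entry (k = 1.2, ρ = 0.7): V_change = 1 + 1.44 − 1.68 = 0.76; V_adj = 1.44 × 0.51 = 0.7344; loss = 1 − 0.7344/0.76 = 3%. For the largest (k = 0.8, ρ = 0.3): V_change = 1 + 0.64 − 0.48 = 1.16; V_adj = 0.64 × 0.91 = 0.5824; loss = 1 − 0.5824/1.16 = 50%.

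**Step 5: where this trial might sit.** For pain, the usual entry threshold of 40 mm on the VAS (Inclusion and exclusion criteria) may narrow the baseline spread. That would lower ρ, which raises the loss, and raise k, which over most of this range reduces it. The two effects pull against each other, so the article's figures do not narrow the range.

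**Step 6: the switch of test.** No arithmetic applies. The rule makes the test depend on the data, and the two tests address different quantities. At about 136 per group a comparison of means is robust to moderate non-normality, so the switch gains little.

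**The case against.** The strongest reply is that nothing here is invalid. Change from baseline is the declared endpoint in Table 2, a two-sample t test on it is unbiased under randomisation, and its interval already reflects chance baseline imbalance. That stands: the issue is efficiency, not bias.

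A reader might infer that the plan throws away a quarter or more of its precision. The article does not support that as a general statement. With equal SDs it needs ρ of 0.5 or less, and at k = 1.2 the loss is below a quarter at all three correlations shown. It is also a variance figure: at ρ = 0.5 the reduction in standard error is 13%.

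A reader might also infer that the secondary outcomes will be complete-case comparisons at weeks 8 and 16, because "Missing data on the primary outcome will be imputed by using the multiple imputation method under the missing-at-random assumption" and no method is given for the others, with planning for "a desired power set at 80%, and accounting for a 20% dropout rate after 4 months". But the article never says complete case, and its abstract says "All outcomes will be analyzed following the intention-to-treat principle". The analysis plan is not shown and may name a method. Silence on this in a condensed article is not a fault, and week 5 would be affected just as weeks 8 and 16 would.

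On the choice of test, the article mentions no formal normality test. Statisticians are blinded, and allocation is revealed only after the analysis is complete, which limits selective choice in favour of one arm. That is a fair mitigation. It does not settle in advance which quantity will be reported.

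**Conclusion.** The point holds as one of efficiency and of a quantity not fixed in advance, on secondary outcomes only. It does not rest on a gap: the article commits to a specific method, and a better one is available from the same data.

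The loss of precision is (1 − ρ)/2 of the variance with equal SDs, or about 10% to 35% for ρ from 0.8 to 0.3. It is about 3% to 50% if k is 1.2 or 0.8 and ρ is 0.3 to 0.7. These are conditional figures, since ρ and the SDs are assumed throughout. The direction is more secure than the size, because (1 − ρk)² cannot be negative.

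The change is worth making before analysis. It is no threat to the trial's primary conclusion: the primary outcome is binary, and its test and sample size do not depend on this rule.

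**What to change.** Replace the rule in Statistics with one pre-specified model for each continuous outcome, with the baseline value and centre as covariates. Either form will do:

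- ANCOVA at each visit, which is enough to recover the precision shown above; or
- a mixed model for repeated measures over weeks 5, 8 and 16, with arm, visit and arm-by-visit terms. This also uses all available visits under the missing-at-random assumption already adopted for the primary outcome. It does not protect against dropout that depends on unobserved values.

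Report the adjusted mean difference with its 95% CI at every visit, whatever the distribution looks like. Keep a rank test, named in advance, as a sensitivity analysis only; it may be useful for skewed measures such as the joint counts.

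The cost is revised wording and slightly more modelling. No extra participants, visits or data are needed.

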### Randomization and allocation

Eligible participants will be randomly assigned in a 1:1 ratio to either the traditional acupuncture group (TA) or the sham acupuncture group (SA). The randomization scheme will be generated by an independent institute, Lnkmed Tech Co. Ltd. (Beijing, China), and the allocation will be performed and concealed through the Interactive Web Response System (IWRS). Stratified permuted block randomization with center-based stratification and variable block size will be applied by Lnkmed using the SAS version 9.4. IWRS will assign a code to each enrolled participant, which will be concealed from participants, outcome assessors and the statisticians. The acupuncturist will be the only one who have access to both the code and the treatment labeled with the code.

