### Recruitment

This study plans to recruit 340 patients with hand OA from six hospitals across Beijing, China. Eligible patients who meet the American College of Rheumatology (ACR) diagnosis criteria of hand OA [23] in the dominant hand will be recruited via WeChat, websites, posters and bulletin boards in the hospitals and nearby communities. The rheumatologist of each center will be in charge of the diagnosis of participants. Informed consent will be adequately explained to all eligible participants. Participants will be asked to sign the consent form before screening, all of them have the right to withdraw their consent at any time and we guarantee the confidentiality of all participants.

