### Interventions

#### TA group

In each center, treatments will be performed by a licensed acupuncturist who have at least 2 years of clinical experience. Before the study starts, the acupuncturists will be extensively trained on the location, depth and angle of acupuncture.

Acupoints are selected in accordance with the meridian theory of traditional Chinese medicine and the consensus of senior doctors, including bilateral Baxie (EX-UE9), bilateral Houxi (SI3), bilateral Waiguan (TE5) and Ashi points. All acupoints will be localized based on the World Health Organization (WHO) Standard Acupuncture Locations as exhibited in Table 1 and Fig. 2. The acupuncturist will first sterilize local skin with 75% alcohol cotton pellets and tape foam pads (Fig. 3), then insert sterile disposable needles (size 0.3 mm × 25 mm) into the acupoints and gently rotate and lift several times to obtain Qi (deqi) response. The depths and angles of needle insertion are shown in Table 1. Every treatment session will last for 30 min, and then, the needles will be gently removed by acupuncturists. Participants will receive three treatment sessions per week (every other day) for 4 consecutive weeks. Using a treatment diary, the treatment sessions will be monitored and assessed.

**Table 1 Tab1:** Locations and manipulations of acupoints

	Location	Depth	Anatomy	Deqi
Baxie (EX-UE9)	Proximal to the web margins between the five fingers at the junction of the red and white skin, 4 points on each hand, 8 in total	0.2–0.5 cun	Interossei muscles	Yes
Waiguan (TE5)	On the posterior aspect of the forearm, 2 cun^a^ proximal to the dorsal wrist crease, midpoint of the interosseous space between the radius and the ulna	0.5–0.8 cun	Between the extensor digitorum and the extensor hallucis longus	Yes
Houxi (SI3)	In the depression proximal to the ulnar side of the fifth metacarpophalangeal joint, at the junction of the red and white flesh	0.2–0.5 cun	Beside the origin of the abductor digiti minimi muscle of hand	Yes
Ashi points	At the midpoint of the dorsum of the most painful joint	0.1 cun	Subcutaneous	No

^a^From the cubital crease to the wrist crease: 12 cun

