### Primary outcome

The primary outcome will be the proportion of responders at week 5. The proportion of responders at week 8 and week 16 will be assessed as secondary outcome. Participants will be defined as “responders” if showing at least 1 of the 3 following criteria: (1) at least a 50% decrease and absolute change from baseline ≥ 20 in visual analog scale (VAS) score on average pain intensity; (2) at least a 50% decrease and absolute change from baseline ≥ 20 in Australian Canadian Osteoarthritis Hand Index (AUSCAN); (3) at least a 20% decrease and absolute change from baseline ≥ 10 in at least two measurements of VAS score, AUSCAN and patient global assessment of improvement. The responder criteria are summarized by the Outcome Measures in Rheumatological Clinical Trials and Osteoarthritis Research Society International (OMERACT-OARSI) [24]. Responders are acknowledged to have clinically active treatment effect [25], since this assessment uses both a relative and an absolute change in three different domains (pain, function and patient’s global assessment) instead of single measurement.

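### Randomisation is stratified by centre, but the only stated test that covers the week-5 responder outcome ignores centre and baseline pain: a small, conservative loss of precision that costs nothing to recover

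*Protocol article*

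**What the plan says.** **Design.** Under Randomization and allocation: "Eligible participants will be randomly assigned in a 1:1 ratio" and "Stratified permuted block randomization with center-based stratification and variable block size will be applied". Centre is the only stratification factor. Under Recruitment: "This study plans to recruit 340 patients with hand OA from six hospitals across Beijing, China".

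**Endpoint.** Under Primary outcome: "The primary outcome will be the proportion of responders at week 5". A responder is defined by relative and absolute change from baseline in pain VAS, AUSCAN and patient global assessment. All three are measured at baseline.

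**Analysis.** Under Statistics: "Categorical variables will be compared using the Chi-square" test or the Fisher exact test. No centre term, covariate, model, effect estimate or confidence interval is mentioned. On the primary outcome itself, that section gives only the analysis set ("The full analysis set will include all randomly assigned patients who received at least one session of treatment") and the handling of missing values ("Missing data on the primary outcome will be imputed by using the multiple imputation method under the missing-at-random assumption"). It does not name a test for the primary outcome, so the chi-square or Fisher test applies by the general rule.

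**The concern.** Stratified allocation balances the arms within each centre and so removes between-centre variation from the treatment comparison. A pooled two-by-two test still counts that variation as noise. Its standard error is then too wide to the extent that centres differ in response, and the precision gained by the design is not used.

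Centre could matter here. Treatment is tied to centre ("In each center, treatments will be performed by a licensed acupuncturist who have at least 2 years of clinical experience"), and the Discussion says the hospitals were chosen to cover a variety of clinics. Operator and case mix may therefore differ by centre.

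Baseline pain is a separate matter. It is not a stratification factor, but it is built into the endpoint: under the 50% pain criterion, a participant starting at 40 mm needs a 20 mm fall and one starting at 80 mm needs a 40 mm fall. If baseline predicts response, using it adds precision from data already collected.

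At stake is some power, not the validity of a positive finding.

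**Working it through.** **1. Reproduce the planned size.** Inputs from Sample size: 83.3% against 69%, two-sided alpha 5%, power 80%, 20% dropout, 1:1 allocation. Unstratified two-proportion formula with unpooled variance:

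n = (1.960 + 0.842)² × [0.833 × 0.167 + 0.69 × 0.31] / (0.833 − 0.69)² = 7.849 × 0.3530 / 0.02045 = 135.5, rounded up to 136 evaluable per arm. Then 136 / 0.8 = 170 per arm.

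This matches the stated figure. The sample size is consistent with an unstratified comparison and does not rely on adjustment.

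**2. Cost of ignoring centre.** The between-centre SD is assumed, because the documents give none. Simulation: 272 evaluable participants, six equal centres, permuted blocks of 4 or 6 within centre, marginal rates as above, 4,000 runs per scenario. Monte Carlo error is about 0.6 points for power and 0.35 points for type I error.

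| Centre SD (logit) | Power, chi-square | Power, CMH by centre | Type I error, chi-square | Type I error, CMH |
|---|---|---|---|---|
| 0 | 79.4% | 79.2% | 4.5% | 4.6% |
| 0.3 | 80.2% | 80.4% | 4.5% | 4.7% |
| 0.5 | 80.2% | 81.1% | 4.4% | 4.7% |
| 0.8 | 80.9% | 82.6% | 3.9% | 4.7% |

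The power differences are −0.2, 0.2, 0.9 and 1.7 points.

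**3. Standard error under the null.** Mean unstratified standard error divided by the actual spread of the estimates:
- SD 0.3: 0.0558 / 0.0551 = 1.013
- SD 0.5: 0.0557 / 0.0549 = 1.015
- SD 0.8: 0.0554 / 0.0529 = 1.047

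The relative noise of an SD from 4,000 runs is about 1/√8,000 = 1.1%. At SD 0, where no excess exists, the ratio came out at 0.0559 / 0.0549 = 1.018. Excesses of 1 to 2% therefore cannot be told from noise; only the value at SD 0.8 is clear. The null runs are the right ones for this comparison: under the alternative, centre effects were redrawn in each run, so the true risk difference itself varied between runs.

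**4. Cost of ignoring baseline severity.** The prognostic strength is also assumed. The adjusted analysis in the simulation was a risk-difference regression on arm, centre and baseline with a robust standard error.

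| Centre SD | Baseline log-odds per SD | Power, chi-square | Power, adjusted |
|---|---|---|---|
| 0 | 0.5 | 80.1% | 81.4% |
| 0 | 1.0 | 80.2% | 85.0% |
| 0.5 | 1.0 | 80.6% | 85.9% |

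With no centre effect and log-odds 1.0, the unadjusted standard error under the null averaged 0.0559 against an actual 0.0564, with type I error 5.1%. Omitting baseline therefore leaves the test correctly sized and costs only precision.

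**5. Link to the imputation.** Rubin's rules combine an estimate and its standard error across imputed data sets. A chi-square statistic alone supplies neither.

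**The case against.** **The primary test is inferred.** The Statistics section states a general rule and names no test for the primary outcome, and an analysis plan that is not shown may already stratify. This stands as a limit on certainty. However, the article does state a method for categorical data, its sample size fits that method, and nothing in it points to a stratified analysis.

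**Centre effects may be small.** All six hospitals are in Beijing, researchers are trained jointly, and the three responder components are patient-reported. An SD of 0.8 is large: around a 69% sham rate it spans about 50% to 83% within one SD. This also stands, and 0.8 should be read as the upper end of the range.

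**The trial may have a margin.** The 20% loss is stated for 4 months, while the endpoint is at week 5. If loss at week 5 were 10% or nil (assumed), the formula in step 1 gives about 84.5% power with 153 per arm or about 88% with 170. It would therefore be wrong to say that the trial has no reserve.

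**Baseline adjustment is optional.** An unadjusted comparison is valid. This is correct, and the gain depends on assumed prognostic strength.

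A reader might infer that the plan's confidence intervals will be wrong or that a significant result could not be trusted. The documents do not support either reading: no interval is specified, and the centre-related error makes the test conservative. Nor does leaving out baseline severity distort the standard error.

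**Conclusion.** The mismatch is real and modest. Randomisation is stratified by centre, while the only stated test applicable to the primary endpoint uses neither centre nor baseline pain.

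- **Centre:** about 0 to 2 points of power for an assumed between-centre SD of 0 to 0.8, with type I error of 3.9 to 4.5%. Nothing is lost if centres do not differ.
- **Baseline severity:** about 1 to 5 points of power for an assumed log-odds of 0.5 to 1.0 per SD, with no effect on the size of the test.

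These figures rest on six equal centres, 136 evaluable per arm and the protocol's response rates. The change is worth making because it is free, not because the stated analysis would be invalid.

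**What to change.** In the Statistics section, name the primary analysis: logistic regression of week-5 response on arm, centre and baseline pain VAS, reported as a risk difference (standardised over the analysis set) with 95% CI. A centre-stratified CMH risk difference is the simpler alternative.

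- Combine the estimate and its standard error over the multiple imputations by Rubin's rules.
- Use the same model for the responder outcomes at weeks 8 and 16 and for the outcome of a decrease of at least 15 points in VAS.
- Keep the unstratified chi-square as a sensitivity analysis.
- Settle the wording before group allocation is revealed.

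The cost is a few lines of text and some programming. The standardised risk difference takes more programming than the stratified one. No new data or participants are needed, and 170 per arm stays as it is.

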### Blinding

In this study, the participants, outcome assessors, and the statisticians will be blinded to the group allocation. The acupuncturists will not be blinded due to the characteristics of acupuncture. Sham acupuncture treatment will mimic the similar sensation of traditional acupuncture treatment using blunt-tip needles. To ensure the success of blinding, the acupuncturists will be discouraged from discussing the treatments or expected results with participants. A blinding assessment will be taken right after the participant’s last session that asks the participant to guess which treatment he/she has received.

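### The abstract promises intention-to-treat for all outcomes, but the primary analysis set leaves out randomised participants who never had a session; bias is possible, not shown, and the set can be redefined in one sentence

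*Protocol article*

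**What the plan says.** The Abstract (Methods) of the protocol article makes a general commitment: "All outcomes will be analyzed following the intention-to-treat principle".

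The Statistics section then fixes the population for the main comparison: "The primary outcome will be assessed in the full analysis set". It defines that population in the next sentence: "The full analysis set will include all randomly assigned patients who received at least one session of treatment". Safety uses the same set. For gaps in the week-5 response, the section says: "Missing data on the primary outcome will be imputed by using the multiple imputation method under the missing-at-random assumption".

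Two other sections describe who knows the arm when treatment starts. Under Randomization and allocation: "The acupuncturist will be the only one who have access to both the code and the treatment labeled with the code". Under Blinding: "The acupuncturists will not be blinded due to the characteristics of acupuncture". The same section states that "the participants, outcome assessors, and the statisticians will be blinded to the group allocation".

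The article does not call the set modified intention-to-treat, give a reason for the exclusion, or plan an analysis of all 340 randomised participants.

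**The concern.** Receiving a first session happens after randomisation. A set that requires it is not the set that randomisation created, so the comparison is protected only if failing to start is unrelated to arm or to outcome. Leaving out never-treated participants is usually defended on the ground that nobody who could influence the start of treatment knew the arm. In this trial that ground is incomplete, because the person who gives the first session, and so completes entry to the primary set, holds the allocation.

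Two things are at stake. The first is labelling: the analysis as defined does not match the principle announced for it. The second is a possible arm-dependent exclusion in the primary comparison, which the plan could close at almost no cost because a method for missing primary outcomes is already specified.

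**Working it through.** **Inputs.** Sample size section: response 83.3% with traditional acupuncture (TA) and 69% with sham acupuncture (SA), two-sided 5% alpha, 80% power, 20% dropout, 170 per arm. The documents do not give the number never treated. The counts *k* below are assumptions: 2, 5, 9 and 17 of 170 are 1.2%, 2.9%, 5.3% and 10% of an arm.

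**1. The plan's own figure.** With unpooled variance:

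n = (1.96 + 0.8416)² × (0.833×0.167 + 0.69×0.31) / (0.833 − 0.69)² = 7.849 × 0.3530 / 0.02045 ≈ 135.5, so 136 per arm.

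136 / (1 − 0.20) = 170. The stated size reproduces. It is a count of randomised participants, so a change of analysis set does not alter it.

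**2. Shift in the planned difference (14.3 points) when *k* = 5 are excluded.** Expected responders: TA 0.833×170 = 141.6; SA 0.69×170 = 117.3.

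| Who is excluded | TA | SA | Difference | Shift |
|---|---|---|---|---|
| Unrelated to arm and outcome | 83.3% | 69.0% | 14.3 | 0 |
| Five non-responders from each arm | 141.6/165 = 85.8% | 117.3/165 = 71.1% | 14.7 | +0.4 |
| Five non-responders from TA only | 85.8% | 69.0% | 16.8 | +2.5 |
| Five non-responders from SA only | 83.3% | 71.1% | 12.2 | −2.1 |

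In the first row the only cost is precision. With complete data, power at the planned rates falls from 87.5% at 170 per arm to 86.5% at 165 (pooled-variance test).

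**3. False-positive risk in the one-sided worst case.** Suppose there is no true effect (69% in both arms) and *k* TA non-responders alone are removed. The spurious difference is 0.69×170/(170 − *k*) − 0.69. The two-sided error is from a normal approximation to the pooled two-proportion test.

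| *k* | Spurious difference | Type I error |
|---|---|---|
| 2 | 0.8 points | about 5.3% |
| 5 | 2.1 points | about 7.0% |
| 9 | 3.9 points | about 12% |
| 17 | 7.7 points | about 34% |

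These are upper limits for each *k*, not predictions.

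**4. Would the planned imputation undo the worst case?** Take *k* = 5 in TA with no week-5 data. If the imputation model contains arm, missing-at-random imputes these five at about the observed TA rate, apart from baseline adjustment: (141.6 + 5×0.858)/170 = 145.9/170 = 85.8%. The estimate does not move. It returns to 141.6/170 = 83.3% only if the five are assessed and found not to respond, or are counted as non-responders. Putting never-treated participants back in the set and relying on imputation alone would correct the label but would hardly change the result.

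**The case against.** The strongest reply has four parts.

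- **The set is openly stated and close to intention-to-treat.** It keeps anyone with even one of 12 sessions, and nobody is removed for poor adherence or later dropout. This is true, and it keeps the point modest. The set still does not match the abstract's commitment, and the article itself fixes it, so it is not a detail left to a later analysis plan.
- **Most failures to start would be the participant's own.** Participants are blinded and have experienced neither treatment before session 1, so their no-shows should not depend on arm. This stands. A reader might infer that the usual defence of excluding never-treated participants is wholly unavailable here; the documents do not support that. Only the acupuncturist's side is open.
- **Nothing gives the acupuncturist discretion to withhold a session.** Diagnosis rests with the rheumatologist, allocation is central, and the Data management and quality control section permits no modification of the intervention. This makes the route less likely. It does not close it, and the Discussion itself lists unblinded acupuncturists as a source of potential bias.
- **The large shifts need an extreme pattern.** A reader might infer that the set inflates the TA rate by 2.5 points, or by 4.7 if nine leave (141.6/161 = 88.0%). Both figures require every exclusion to be a TA non-responder with none from SA. Nothing in the documents suggests that pattern, and the reverse pattern would work against TA.

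**Conclusion.** The mismatch is certain on the text: the article announces intention-to-treat for all outcomes and then defines a modified intention-to-treat set for the primary one, without an all-randomised analysis beside it.

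Bias is possible, not shown. Its size depends on an unstated number of never-treated participants and on why they did not start. With five assumed exclusions per affected arm and the planned response rates, it runs from zero (unrelated to arm and outcome), through about 0.4 points (non-responders from both arms), to about 2.5 points in the worst case against a planned difference of 14.3. If hardly anyone fails to start, the effect is negligible.

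The change is still worth making, because it is cheap, closes an avoidable route and makes the primary analysis match its description.

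**What to change.** - Define the primary efficacy set as all randomised participants, analysed in the arm to which they were allocated.
- Seek the week-5 assessment in participants who never start treatment. The Secondary outcomes section times assessments from randomisation, so this is feasible within the schedule.
- Use the planned multiple imputation only where that assessment is missing. Add a sensitivity analysis that counts never-treated participants without data as non-responders, since imputation alone would leave the estimate almost where it was.
- Keep receipt of at least one session as the definition of the safety set and, if wanted, as a sensitivity set for efficacy.
- Report participants with no session by arm, with reasons.

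Cost: one redefined sentence and one added sensitivity analysis, a few more imputed outcomes, and possibly a slightly smaller estimated effect. The sample size of 170 per arm is unchanged.
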